# Addition of a new three-dimensional adjustable cervical thoracic orthosis to a multi-modal program in the treatment of nonspecific neck pain: study protocol for a randomised pilot trial

**DOI:** 10.1186/s13063-019-3337-0

**Published:** 2019-04-29

**Keywords:** Neck pain, Ambulatory, Orthotic

## Abstract

**Background:**

Nonspecific neck pain (NSNP) is one of the most common musculoskeletal problems treated by orthopaedic physicians and physiotherapists. Posture has emerged as one of the major risk factors associated with NSNP, but most previous studies ignored correct posturing as an effective treatment. Therefore, one of the major challenges faced by clinicians is how to incorporate 3D posture findings into the treatment plane. The present study will evaluate the feasibility of conducting a larger randomized trial. This pilot study is designed to investigate the hypothesis that a multimodal programme supplemented with the addition of a 3D adjustable cervico thoracic posture corrective orthotic (CTPCO) will yield short- and long-term improvement on NSNP management outcomes.

**Methods/design:**

This pilot, single-blind, randomized controlled trial will divide 24 patients into two groups (study and control) using block randomization. Both groups will receive conventional treatment consisting of a moist hot pack, soft tissue mobilization, manual therapy and therapeutic exercise. The study group will undergo ambulatory mirror-image functional re-training wearing a 3D adjustable CTPCO. The primary outcome is feasibility, including recruitment (e.g., time to complete enrolment, recruitment rate), patient retention and adherence to treatment allocation (e.g., session attendance, home practice, use of non-study treatments). The secondary outcomes used to assess the effectiveness of the treatment will include neck pain (measures using the visual analogue scale (VAS)) and neck disability (measures using the neck disability index (NDI)), among other outcome measures, compared between the experimental and control groups. Three-dimensional posture parameters of head measurements will be provided by a Global Posture System (GPS). The outcome measures for determining the treatment effect will be assessed at three intervals: pre-treatment, after 10 weeks of intervention and after 3 months at follow-up.

**Discussion:**

This randomized controlled pilot trial will inform the design of a future full-scale trial. The outcomes will provide some resources for the incorporation of ambulatory mirror-image functional re-training intervention compared to a control group intervention for neck pain, disability and 3D posture parameters.

**Trial registration:**

Prospectively registered at ClinicalTrials.gov, NCT03331120. Registered on 22 October 2017.

**Electronic supplementary material:**

The online version of this article (10.1186/s13063-019-3337-0) contains supplementary material, which is available to authorized users.

## Background

Nonspecific neck pain (NSNP) is one of the most common musculoskeletal problems treated by orthopaedic physicians and physiotherapists [1, 2]. NSNP has an annual incidence rate of 38 to 73% and a lifetime prevalence of approximately 48%, leading to both economic and social problems [3, 4].

Posture has emerged as a major risk factor associated with NSNP [5–8], but most previous studies have ignored correct posturing as an effective treatment. The few studies that used posture corrective strategies were based on a dated concept that did not incorporate the 3D nature of posture into the treatment strategy [9–12]. Therefore, one of the major challenges faced by clinicians is how to incorporate 3D posture findings into the treatment plan.

Harrison and colleagues [13] reported that posture problems occurred in the head, ribs and pelvis in three dimensions in the form of translations and rotational displacements. Therefore, we should consider three-dimensional postural assessment and correction during the treatment of NSNP to obtain long-lasting effects and prevent the recurrence of neck pain.

Several tools are available for objective postural measurements in clinical use, including simple plumb line measure, photographic techniques [14–16], moiré topography [17] and various computer-assisted methods, such as electro goniometers [18]. These methods are used in clinical assessments, but they have limitations, including the inability to measure neck posture as rotations and translations in six degrees of freedom, as mentioned by Harrison and colleagues [13].

The current study will use a 3D analysis system called the Global Postural System (GPS) [19–21], which is a novel device that investigates all postural variables at once and provides the managing physiotherapist with radiation-free and accurate measurements [16]. This device also provides further information about foot pressure analysis and other 3D features that allow bracing designs to be tailored for each patient [20].

Numerous studies have shown that mirror images in motion exercises, which are prescribed specifically to help normalize the patient’s neuromuscular dysfunction and postural deformation via reflecting the patient’s posture across different planes, are more beneficial than a less personalized programme [22–24].

With these considerations in mind and to integrate the findings of 3D postural assessment into the treatment programme, we designed an adjustable cervico thoracic posture corrective orthotic (CTPCO) to be worn by the patient for a short time. The device has the ability to reflect all transitional displacements and rotational movements of the head. Ambulatory exercises will be performed using a treadmill while the CTPCO holds the patient’s reverse posture.

We designed a randomized two-arm pilot trial to investigate the hypothesis that the addition of a 3D adjustable CTPCO to a multimodal programme will produce short- and long-term improvement effects on NSNP management outcomes (i.e., neck pain, neck disability and 3D posture parameters of the head).

The primary aim of this study is to evaluate the feasibility of conducting a larger randomized trial that considers recruitment, compliance to study protocols and adverse events. The secondary aim is to investigate the effect size of the addition of ambulatory mirror image functional re-training via the wearing of a 3D adjustable CTPCO compared to control group interventions for neck pain, disability and 3D posture parameters.

## Methods/design

### Study design

The study will be a single-blind superiority pilot randomized control trial (RCT) with two parallel groups. The study will be performed according to SPIRIT [25] and good clinical practice guidelines (SPIRIT checklist, Additional file 1). The Ethical Committee of Tongji Hospital, Tongji Medical College, Huazhong University of Science and Technology (HUST), Wuhan, China approved the study protocol (certificate of approval number TJ-IRB20170703), which is prospectively registered at ClinicalTrials.gov (NCT03331120). The study will be performed in the Rehabilitation Department at Tongji Hospital, Affiliated with HUST, China.

## Procedures

Potential patients will be recruited through advertisements in clinical waiting rooms and via mobile patient recruitment applications, like Wechat (Tencent Ltd, Shenzhen, China). Eligible patients will be 17 to 40 years of age with a history of neck pain for longer than 3 months and who are interested in taking part in a clinical trial of physical therapy. No details of radiographic features of the neck region will be mentioned in the advertisements. Volunteers will contact the project coordinator or physician of the rehabilitation clinic and will undergo an initial screening. A clinical and radiological examination will be used to exclude the presence of a specific cause of neck pain.

Patients will complete a written, informed consent form, provide demographic data and complete a survey of patient-reported outcome measures. An outcome assessor will measure the rotational movements and translational displacements of the head in relation to the thoracic region using GPS.

Following the baseline assessment, a research assistant will randomize patients to a study group and control group using sealed, numbered envelopes and a randomisation list generated by the “random integer generator” (https://www.random.org/integers/). The randomisations will be restricted to permuted blocks of different sizes. Each random permuted block will be transferred to a sequence of consecutively numbered, sealed, opaque envelopes for storage in a locked locker until required. As each patient formally enters the trial, the researcher will open the next envelope in the sequence in front of the patient. A blinded investigator will perform all outcome assessments at baseline, after 10 weeks of intervention and after 3 months of follow-up.

## Eligibility

### Inclusion criteria

Male and female subjects age from 17 to 40 yearsNeck pain with equal or greater than 3/10 on a visual analogue scale (VAS) and pain lasting more than 3 months (chronic neck pain) [26, 27]Patients with neck disability; this is defined by a score of at least 5 (on a 50-point scale) on the neck disability index (NDI) [28]Patients will be included if they have posture abnormalities by screening test using GPSSubjects must be able to continue treatment for 10 weeks and then attend 3-month follow-upIf patients can accept and sign informed consent form

### Exclusion criteria

If patient report any of the following conditions:Neck pain associated with whiplash injuries, medical red flag history (such as tumour, fracture, metabolic diseases, rheumatoid arthritis and osteoporosis) [27].Neck pain with cervical radiculopathy or neck pain associated with externalized cervical disc herniation [27]Fibromyalgia syndrome; to avoid the similarity of fibromyalgia with a NSNP diagnosis, a physician will use the criteria for the clinical diagnosis of fibromyalgia according to the American College of Rheumatology [29]If the patient had previous surgery in the neck area (irrespective of the reason for the operation) [27]Neck pain accompanied by vertigo caused by vertebra basilar insufficiency or accompanied by non-cervicogenic headaches [27]People will also be excluded if they are undergoing any type of pain treatment or they have psychiatric disorders or other problems that contraindicate the use of the techniques in this study [27]If patient has true leg length discrepancy and an associated pathology of upper and lower limbs that may interfere with the global posture (e.g., foot, knee or hip deformities)The patients will be unable to attend a 10-week treatment programme and follow-up assessments after 3 months

### Interventions

Twenty-four patients will be randomized into two groups (study and control) using block randomization. Both groups will receive conventional treatment consisting of a moist hot pack, soft tissue mobilization, manual therapy and therapeutic exercises.

The study group will also undergo ambulatory mirror-image functional re-training via the wearing of a 3D adjustable CTPCO. Patients in both groups will attend 30 physical therapy treatment sessions over a 10-week period at three sessions per week and then follow-up after 3 months. Short-term follow-up evaluations will be performed after 10 weeks of interventions, and the long-term follow up will be performed 3 months after the end of the 10 weeks of treatment. The flow diagram for this trial is presented in Fig. 1.

**Fig. 1 Fig1:**
[figure not shown]
The flow diagram for this trial

### Conventional treatment

A moist hot pack will be applied to the area of pain in neck region muscles, like the upper part of the trapezius, levator scapulae, splenius capitis and cervicis muscles, for 15 min prior to other conventional treatments to improve the effectiveness of the treatment and reduce short-term pain and disability [30].

Soft tissue mobilization—a deep stroking massage—will be performed along the entire length of the taut band within the following muscles: upper part of the trapezius, supraspinatus, levator scapulae, splenius capitis and cervicis muscles [31].

### Manual therapy

The protocol of Beltran-Alacreu et al. [27] consists of specific passive movements in the facet cervical joints, global mobilization of the cervical spine and a high-velocity technique in the dorsal region. All of these techniques have been proven in previous studies to reduce neck pain and improve joint function of the cervical spine [32, 33].

### Therapeutic exercise

We will create therapeutic exercise programmes for stretching protracted or rounded shoulder muscles and posterior neck muscles in addition to strength exercises of shoulder retractor muscles and the deep cervical flexors, consistent with the protocol described by Harman et al. [12] (Additional file 2).

All of the multimodal programme components will be repeated three times per week for 10 weeks in both groups. All patients will complete the multimodal programme at our physiotherapy clinic.

### Cervico thoracic posture corrective orthotic

The CTPCO is a low-profile, lightweight, thermoplastic orthotic that is easily applied and removed by the patient. This brace is adjustable and consists of two parts: one part is attached to the thoracic region and is considered a fulcrum on which the other part, which is attached to the head, will be moved. The two parts are connected to each other by a movable joint which allows the movable part to be adjusted in all translational and rotational movements. The brace will reverse (overcorrect) the abnormal posture according to the 3D posture analysis data. The device permits movement in all directions as shown in Fig. 2.

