### Ambulatory mirror-image functional re-training via wearing of the 3D adjustable CTPCO

The patient will use the adjustable CTPCO and walk at an approximate speed of 2–3 miles per hour on a standard, motorized treadmill for 20 min, three times per week for 10 weeks. The brace will reverse (overcorrect) the abnormal posture according to the 3D posture analysis data. The facilitation of tissue remodelling using reverse posture training is called mirror-image exercise. An additional movie file shows this procedure in more detail (Additional file 3).

**Additional file 3:** Movie file showing ambulatory mirror image functional re-training through wearing a 3D adjustable CTPCO. (MP4 134029 kb)

The same physiotherapist will individually deliver the entire intervention programme. The physiotherapist has had 10 years of experience and received training in these manual techniques, thereby minimizing inter-therapist variation and increasing reliability.

Patients in both groups will be instructed to perform neck retraction/extension, scapular retraction and deep upper cervical flexor strengthening exercises at home, twice daily as their home routine. To accurately monitor the exercise times and the number of sets performed during the study, a pamphlet illustrating the exercises and a record sheet will be distributed to the patients.

The record sheets will be collected every week and analysed to calculate the mean exercise frequency per week and the mean exercise time per day. The record sheet analysis will reflect a high degree of compliance with the home exercise sessions.

Patients will be encouraged to practice the same home routine at least twice per week for up to three months after treatment, but the ambulatory mirror image functional re-training will be terminated after the initial 10 weeks or 30 visits of intervention. Patients will be contacted via the wechat application every 3 days to gather the record sheet and to inspire patients to continue the training.

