### Data collection

The primary outcome in the present study will be measured as the feasibility outcomes of conducting an RCT. The secondary outcome will be measured by the visual analogue scale (VAS), neck disability index (NDI) and the 3D posture parameters measured by the GPS device. The primary and secondary outcomes will be measured at baseline, after 10 weeks and after 3 months of follow-up. The schedule of treatment and outcome assessments is presented in Table 1.

**Table 1 Tab1:** Schedule of treatments and outcome measures throughout the trial

	Baseline 0 weeks	Treatment period 10 weeks	Follow-up after 3 months
Measures			
Feasibility outcomes	√	√	
VAS	√	√	√
NDI	√	√	√
3D posture parameters	√	√	√
Treatments			
Ambulatory mirror image functional re-training through wearing 3D adjustable CTPCO		√	
Conventional treatment like moist hot pack, soft tissue mobilization, manual therapy, therapeutic exercise		√	

*VAS* visual analogue scale, *NDI* Neck Disability Index, *3D* three-dimensional, *CTPCO* cervico thoracic posture corrective orthotic

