### Measured items (the postural parameters) of the head region in relation to the thoracic region

A right-handed Cartesian coordinate system with x-axis positive to the left, y-axis positive vertically and z-axis positive to the anterior will be used to describe postures of the head as translations or displacements in centimetres (Tx, Ty, Tz) along these axes and as rotations (Rx, Ry, Rz) in degrees from a normal upright stance. Vertical translations (Ty), which would require radiographic analysis of hypo- or hyper-lordosis, will not be calculated in the present study (Fig. 6) [13].

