### Postural translations of the head

Tx (right or left side shifting or lateral translation): measure horizontal distance from the ideal plumb line passing through middle sternal notch to vertical line passing through nose.Tz (anterior or posterior translation): measure horizontal distance from the vertical line crossing the middle acromion process to the vertical line crossing the external ear.

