### Statistical analysis

Results of primary outcome measures will be provided descriptively in tables and compared to the a priori established goals. To provide a recommendation for estimated sample size for a future full-scale RCT, between-group effect sizes and 95% confidence intervals (CIs) with Hedges correction will be calculated for changes in the secondary outcomes of VAS, NDI and 3D posture parameters. The mean ± standard deviation score for each of the subscales will be used in the calculation of the effect size. Estimated sample size will be determined using the between-subject effect size, with a minimum of 80% power (*α* = 0.05). The sample size will be increased to allow for an estimated 20% dropout rate. Statistical methods for the secondary outcome measures will be evaluated via comparisons of changes between groups. Complete case analyses will be performed to include outcomes from all patients who completed baseline and follow-up evaluations, as recommended in the Consolidated Standards of Reporting Trials (CONSORT) guidelines [39]. The between-group difference in change scores for each outcome measure from baseline to follow-up will be determined and reported as the means and 95% CI, using an analysis of covariance. Covariates of age and sex will be included in the analysis. All statistical analyses will be performed in SPSS version 23.0 software (IBM Corporation, Armonk, NY) with significance set at *P* < 0.05.

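### Head posture is recorded on signed axes around neutral but analysed as plain change, so the posture effect size does not measure correction

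*Protocol article*

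**What the plan says.** - **Action of the brace.** The section on the orthotic, and again the section on ambulatory re-training, states: "The brace will reverse (overcorrect) the abnormal posture according to the 3D posture analysis data".
- **Exposure.** "Patients in both groups will attend 30 physical therapy treatment sessions over a 10-week period at three sessions per week"; the braced walking takes place "on a standard, motorized treadmill for 20 min, three times per week for 10 weeks".
- **Scale of the posture outcomes.** Under Measured items: "A right-handed Cartesian coordinate system with x-axis positive to the left, y-axis positive vertically and z-axis positive to the anterior will be used". Deviations are expressed relative to a normal upright stance. The sections on translations and rotations define each parameter in both directions, for example "Tx (right or left side shifting or lateral translation".
- **Timing.** "The primary and secondary outcomes will be measured at baseline, after 10 weeks and after 3 months of follow-up".
- **Analysis.** Hedges-corrected between-group effect sizes "will be calculated for changes in the secondary outcomes of VAS, NDI and 3D posture parameters", and "The between-group difference in change scores for each outcome measure from baseline to follow-up will be determined", by analysis of covariance with age and sex as covariates. The section does not say whether posture change is the raw signed difference, the difference aligned to each patient's baseline deviation, or the change in distance from neutral.

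**The concern.** For VAS and NDI, a larger fall is always better, so mean change is a sound measure of benefit. For a head-posture parameter it is not. The target is neutral, a patient can stand on either side of it, and the intervention is designed to push beyond it. A mean change then mixes three different things: movement towards neutral, movement past neutral, and the accident of which side patients started on.

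Posture is one of the three outcome domains named in the hypothesis, and its effect sizes are among those meant to support a sample-size recommendation. If the score does not track correction, the pilot may report a posture effect that is inflated by reversals or cancelled by a left-right mix, and the reader of the summary could not tell which.

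**Working it through.** **The plan's own figure.** 3 sessions per week x 10 weeks = 30 sessions, as stated.

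**Inputs.** From the article: signed axes, deviation possible on both sides, analysis on change, 24 patients. Assumed: 12 per arm, and a baseline deviation of 3 cm, since the article gives no posture values.

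**Step 1: one patient, baseline b = +3 cm, end value e.**
- Signed change in the direction of correction: b - e.
- Change in distance from neutral: |b| - |e|.

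| End value (cm) | Signed change (cm) | Change in distance from neutral (cm) |
|---|---|---|
| 0 (full correction) | 3.0 | 3.0 |
| -1.5 | 4.5 | 1.5 |
| -3 (mirror image) | 6.0 | 0.0 |
| -4.5 | 7.5 | -1.5 |

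Signed change gives the mirror image twice the score of full correction. Distance from neutral gives it no improvement.

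**Step 2: an arm of 12 with the raw axis value (end minus baseline), every patient starting 3 cm from neutral.**

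| Left / right at baseline | All fully corrected: mean change (SD) | All fully reversed: mean change (SD) |
|---|---|---|
| 12 / 0 | -3.0 (0) | -6.0 (0) |
| 9 / 3 | -1.5 (2.71) | -3.0 (5.43) |
| 6 / 6 | 0.0 (3.13) | 0.0 (6.27) |

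The same perfect correction in every patient yields a mean of -3.0, -1.5 or 0.0 cm, depending only on the side from which patients started. In the evenly mixed arm the mean equals that of an arm in which nobody moved, so the difference from an unchanged control arm is 0. On distance from neutral, every row gives 3.0 cm for full correction and 0.0 cm for full reversal.

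**Step 3: partial overshoot, all 12 starting at +3 cm.** Suppose 8 end at 0 and 4 end at -3 cm (assumed).
- Signed change: (8 x 3 + 4 x 6)/12 = 48/12 = 4.0 cm, which is 33% above the 3.0 cm obtained if all 12 end at 0.
- Distance from neutral: (8 x 3 + 4 x 0)/12 = 24/12 = 2.0 cm.

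**Sensitivity.** With an assumed baseline deviation of 1 to 5 cm instead of 3, the mirror image scores 2 to 10 cm on signed change and 0 on distance from neutral. The pattern does not depend on the 3 cm.

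**Step 4: what a mean still hides.** On distance from neutral, +3 to -2 cm gives 3 - 2 = 1 cm of improvement. The overshoot is penalised (1 cm instead of 3 cm), but the mean does not show that the patient changed sides. A count is needed for that.

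**The case against.** The strongest reply is that the article never says overshoot counts as benefit. It speaks only of changes; how a derived variable is scored is often left to an analysis plan, and distance from neutral may be what is intended. This stands in part: a reader might infer that crediting overshoot is planned, and the text does not support that. But the stated rule, change from baseline for a parameter on a signed axis, fails on its literal reading whether patients deviate to the same side or to both. That is a poorly chosen rule, not just an omitted detail.

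Other tempting readings should also be resisted:
- **The brace runs on baseline data for all 30 sessions (30 x 20 = 600 min, or 10 h).** The 10-week and 3-month readings are an outcome schedule. The brace is adjustable and the article is silent on resetting it. Silence does not show a frozen setting, and the outcome schedule does not contradict the brace sections.
- **Reversal cannot be seen.** It can: each patient's signed readings would show it. Adverse events are also part of the primary aim, and unacceptable risk of serious events can end the trial. What is missing is a planned summary of reversals.
- **Forward head position (Tz) deviates only one way.** The article defines it as anterior or posterior.
- **The brace leaves a lasting reverse deviation.** Nothing in the article shows this. The point is about scoring and does not depend on it.

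Finally, the future trial's primary outcome is to be chosen among patient-reported measures, so posture cannot become that outcome. This limits the consequence. It does not remove it, because posture effect sizes are still to be calculated and reported for planning.

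**Conclusion.** The point holds as a flaw in the analysis rule for the posture outcomes. Plain change is the wrong score for a parameter whose best value is in the middle, especially with a device intended to go past that value. On signed change with a common direction, a full mirror-image reversal scores twice full correction, and 4 reversals among 12 raise the mean by 33%. On raw signed values with an even left-right mix, correction and reversal both average 0. These sizes rest on assumed deviations, 12 patients per arm and an assumed share of reversals; the article gives no posture data, so the size in this trial cannot be stated. The pain, disability and feasibility outcomes are not affected. The change is worth making before the posture data are analysed.

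**What to change.** 1. In the Statistical analysis section, define posture improvement for each parameter as the change in absolute deviation from neutral, with the neutral value named for that parameter. Use this score for the change scores, the analysis of covariance and the Hedges effect sizes, so that movement past neutral is not counted as improvement.
2. From the readings already taken at 10 weeks and 3 months, report by arm and parameter the number of patients whose deviation has crossed to the opposite side by more than a pre-specified margin, and how many of those seen at 10 weeks persist at 3 months. The article gives no measurement error for the posture system, so the margin has to be chosen and justified in advance.

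**Cost.** One definition and one extra table; no new visit or measurement. The posture effect may look smaller. No brace setting or adjustment rule is proposed.
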